### Eligibility criteria

Eligible patients will meet all the following inclusion criteria: (1) Men or women aged 50 years and older (with no upper age limit); (2) Fracture of the femoral neck confirmed with anteroposterior and lateral hip radiographs, computed tomography, or magnetic resonance imaging (MRI); (3) Operative treatment of displaced fractures within 4 days of presenting to the emergency room, or operative treatment of undisplaced fractures within 7 days of presenting to the emergency room; (4) Patient was ambulatory prior to fracture, though they may have used an aid such as a cane or a walker; (5) Anticipated medical optimization for operative fixation of the hip; (6) Provision of informed consent by patient or a legally appointed representative; (7) No other major trauma (defined as an Injury Severity Score >16); and (8) Low energy fracture, in the judgment of the attending surgeon.

We will exclude patients meeting any of the following criteria: (1) Patients not suitable for internal fixation (i.e., severe osteoarthritis, rheumatoid arthritis, or pathologic fracture); (2) Associated major injuries of the lower extremity (i.e., ipsilateral or contralateral fractures of the foot, ankle, tibia, fibula, knee, or femur; dislocations of the ankle, knee, or hip; or femoral head defects or fracture); (3) Retained hardware around the affected hip; (4) Infection around the hip (i.e., soft tissue or bone); (5) Patients with disorders of known bone metabolism except osteoporosis (i.e., Paget’s disease, renal osteodystrophy, osteomalacia); (6) Patients with a history of frank dementia that would interfere with assessment of the primary outcome (i.e., revision surgery at 24 months); (7) Likely problems, in the judgment of the investigators, with maintaining follow-up (i.e., patients with no fixed address, report a plan to move out of town, or intellectually challenged patients without adequate family support); and (8) Exclusion of a patient because of enrolment in another ongoing drug or surgical intervention trial will be left to the discretion of the attending surgeon, on a case-by-case basis.

### Patient recruitment and screening

Data will be collected from academic hospitals in Australia, Canada, England, Germany, India, Norway, The Netherlands, and The United States. A complete list of clinical sites can be obtained from the corresponding author upon request. All patients presenting to participating surgeons with a diagnosed femoral neck fracture will be screened. Figure 1 shows the patient identification and screening procedures. Informed consent will be obtained from all eligible patients by qualified clinical site personnel who are knowledgeable about the study. If a patient lacks capacity and is deemed unable to consent, informed consent may be obtained from the patient’s legally authorized representative.

**Figure 1 F1:**
[figure not shown]
Recruitment schedule (Baseline radiographs & Data collection).

We will enroll all patients who meet the eligibility criteria and document reasons for failure to randomize all eligible patients. We will also document all patients screened for eligibility and record them as: (1) Eligible and included; (2) Eligible and missed; or (3) Excluded. The Central Adjudication Committee (CAC) will adjudicate all situations where eligibility is in doubt.

### Study interventions

#### *Cancellous screw*

Patients allocated to the cancellous screw group will receive multiple threaded screws (with a minimum of 2 screws and a minimum diameter of 6.5 mm). Surgeons will be allowed to use any threaded screw or hook pin (i.e., Gouffon, Uppsala, von Bahr, Hansson hook pins, etc.) or cancellous threaded screw (i.e., cannulated or non-cannulated, Ace, AO/Anklylosing Spondylitis International Federation (ASIF), Asnis, Richards, etc.). Surgeons will follow the technique guides associated with the screw manufacturers. No injectable bone substitutes will be allowed for augmentation of the implant fixation. Surgeons will document the following: (1) Number of screws; (2) Number of washers; (3) Manufacturer; (4) Reduction technique; (5) Decision to perform a capsulotomy or aspirate intracapsular hematoma; and (6) Screw configurations, especially of the third screw (outside of 2 critical placements inferiorly and posteriorly).

#### *Sliding hip screw*

Patients allocated to the sliding hip screws group will receive a single larger diameter partially threaded screw affixed to the proximal femur with a side plate (with a minimum of 2 holes and a maximum of 4 holes) and no supplemental fixations. Surgeons will be permitted to use any commercially available sliding hip screw implant (i.e., Stryker, DePuy, Synthes, Smith and Nephew, Zimmer, etc.), and will insert implants as per the manufacturers’ technical guides. The derotational kirschner wire should penetrate the acetabulum to provide maximal resistance to torsion. A centre-to-centre approach is recommended, while avoiding a superior and anterior approach. Spiral blades and helical screws are permitted, because they function similarly to the sliding hip screw. It will be documented when spiral blades and supplemental/derotational screws are employed by the surgeon.

The use of a compression screw, manufacturer, reduction technique, decision to perform a capsulotomy, aspiration of intracapsular hematoma, and final screw position measured by the Tip Apex Distance will be documented and based upon surgeon preference. No injectable bone substitutes will be allowed for augmentation of the implant fixation.

### Standardization of procedures and peri-operative care

We will recommend that clinical sites standardize key aspects of peri-operative care including: (1) Pre-operative antibiotics (i.e., cephalosporins, or equivalent coverage) administered before surgery and continued for 24 hours post-operatively; (2) Pre-operative thromboprophylaxis (i.e., Thromboembolic Disease (TED) Stockings, pneumatic compression boots, or medical prophylaxis discontinued in sufficient time to allow surgery as guided by International Normalized Ratio (INR)/Partial Thromboplastin Time (PTT)); (3) Post-operative thromboprophylaxis with unfractionated Heparin, Low Molecular Weight Heparin (LMWH), Warfarin, anti-platelet agents, or intermittent pneumatic compression boots.

Post-surgery, we will recommend that patients will be weight-bearing as tolerated and then advanced according to the attending surgeon’s best judgment (i.e., we will permit touch weight-bearing for displaced fractures and then advanced weight-bearing according to the surgeon’s best judgment).

We will recommend that all patients in the study receive 600 mg of Calcium by mouth (PO) daily and/or vitamin D 1000 International Units (IU) per day (provided there are no contraindications), or further investigation and treatment of osteoporosis as recommended by a local osteoporosis expert/consultant as necessary. Appropriate nutritional assessment with administration of oral micronutrient feeds will also be provided as needed.

Patient positioning, fracture reduction, and surgical exposure in the operating room will not be standardized as these are highly variable across the world. However, to ensure similar peri-operative care regimens it will be recommended that participating centres standardize these aspects of patient care. Finally, due to a lack of evidence favouring a particular approach, the following will be recorded but not standardized: (1) Use of pre-operative traction; (2) Surgical delay; (3) Type of anesthetic (i.e., general versus regional); and (4) Physiotherapy and rehabilitation programs. All patients in the study will receive medical consultation to optimize condition prior to surgery.

### Study outcomes

#### *Primary study endpoints*

The primary study endpoint is re-operation within 24 months post initial surgery to promote fracture healing, relieve pain, treat infection, or improve function including the following: (1) Implant removal prior to fracture healing; (2) Revision surgery with another internal fixation implant; (3) Revision surgery to arthroplasty; and (4) Soft tissue procedures, especially incision and drainage for deep infection at the bone implant interface. Classification of the reason for revision surgery is as follows: (1) Implant failure (2) Superficial or deep infection ; (3) Avascular necrosis; (4) Hip instability; (5) Hip dislocation; (6) Open wound; (7) Painful hardware; (8) Intractable pain due to wear of the acetabulum; (9) Peri-prosthetic femur fracture; and (10) Nonunion. Other classifications will be used if applicable. Planned revision surgeries will not be considered study events (i.e., technical malreduction requiring early revision). Criteria for the diagnosis of nonunion will include a failure of the fracture to progress towards healing for at least 2 months on consecutive radiographs. This will be evident as a persistent fracture line on radiograph, continued pain with hip range of motion, and the inability to weight-bear without pain. Avascular necrosis will be defined as a process that is characterized pathologically by bone marrow ischemia and eventual death of trabecular bone. Infection will be classified according to the Center for Disease Control Criteria [29].

Our choice of a 24 month follow-up period is dictated by the following 2 factors: (1) We have established a consensus among participating surgeons that the decision to re-operate on the hip fracture would occur within the first 24 months following surgery in all, or virtually all, patients and (2) Previous studies have reported 100% of revision surgeries occurring between 2 and 12 months for undisplaced fractures and 70-100% in 24 months for displaced fractures. Although nonunion and avascular necrosis may be present after 24 months, previous studies suggest that 70-98% of revisions due to nonunion and avascular necrosis occur within 24 months [30,31]. Thus, we can expect that nearly all the revision surgeries will occur within 24 months.

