### Adjudication of study events

The CAC is comprised of a Chairperson plus three orthopaedic surgeon committee members. The CAC is responsible for assessing patient eligibility (if in doubt) and they will independently adjudicate radiographic characteristics and quality of the surgery, fracture healing, revision surgeries, fracture-related complications (i.e., avascular necrosis, nonunion, malunion, implant breakage or failure, infection), and mortality. The adjudicators may review the patients’ case report forms and x-rays and determine if the reported outcome meets the criteria for being a study event. Any disagreements between the adjudicators will be discussed and resolved during consensus conference calls with the CAC. If consensus cannot be reached after extensive discussion, a vote will be permitted at the discretion of the Chair. All decisions made by the committee will be final. The CAC members will not be blinded to treatment as it is not possible to accurately judge blinded images; however, they will be blinded to the name and location of the clinical site.

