One limitation of the FAITH trial is the inability to blind patients, surgeons, and outcome adjudicators. Patients cannot be blinded as the two devices leave unique scarring patterns and surgeons cannot be blinded as the devices are easily discernible. It was planned that outcome adjudicators would be blinded to study treatment arm by digitally superimposing cancellous screws and the sliding hip screw on the same x-ray image for the assessments of quality of fracture reduction, fracture healing, infection, and avascular necrosis. However, after piloting this approach we found that it was still possible to often correctly identify the true treatment, and that difficulties with adjudication were created because of too much bone being covered. Therefore this approach was found to be infeasible for adjudicating and as a result outcome adjudicators will not be blinded to study treatment during their assessment of patients’ radiographic characteristics and quality of surgery. However, as revision surgery (the primary outcome) is objective, it is expected that a lack of blinding will not introduce significant threats to validity. To limit the minimal risk of bias that unblinded adjudication can create, a CAC will be used and consensus will be required on all adjudication events.

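### Early re-operation for malreduction is taken out of the primary endpoint by adjudicators who know the treatment arm, a step that the plan's objectivity argument does not cover

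*Protocol article*

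**What the plan says.** In the protocol article, under Primary study endpoints, the definition is: "The primary study endpoint is re-operation within 24 months post initial surgery to promote fracture healing, relieve pain, treat infection, or improve function". The listed procedures include "Revision surgery with another internal fixation implant" and revision to arthroplasty. Time runs from the initial surgery and no early window is left out. The same paragraph then adds: "Planned revision surgeries will not be considered study events (i.e., technical malreduction requiring early revision". It does not say what makes a revision planned, how early is early, or when the plan must have been recorded.

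Under Adjudication of study events, the Central Adjudication Committee (CAC) reviews revision surgeries and quality of surgery, and its members "determine if the reported outcome meets the criteria for being a study event". The section also states: "The CAC members will not be blinded to treatment as it is not possible to accurately judge blinded images". Members are blinded to site only. If consensus fails, "a vote will be permitted at the discretion of the Chair", and "All decisions made by the committee will be final".

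The Discussion lists unblinded adjudication as a limitation and answers it thus: "as revision surgery (the primary outcome) is objective, it is expected that a lack of blinding will not introduce significant threats to validity".

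**The concern.** That a patient returned to theatre is a fact that needs no judgement. Whether the return was for technical malreduction, and so does not count, is a judgement about the quality of the reduction. The exclusion makes primary event status depend on it. The Discussion itself says that blinding had been intended for the assessment of reduction quality and was dropped because it did not work.

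If adjudicators apply the rule more readily in one arm, or if such re-operations are more common in one arm, events leave the primary comparison unequally. That can create or hide a treatment difference, in a direction that cannot be known beforehand. At stake is bias in the primary hazard ratio; the loss of power is small.

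**Working it through.** **1. The texts side by side.**
- A re-fixation soon after surgery because the reduction was poor can satisfy the endpoint's purpose (healing, pain, function) and its procedure list. It also fits the exclusion. The endpoint section gives no rule to separate the two.
- Under Minimizing co-intervention and contamination, patients switched to arthroplasty during the operation are excluded only if the CAC finds that the decision could not plausibly be linked to allocation. The malreduction exclusion has no such test.
- Under Standardization of procedures and peri-operative care, fracture reduction is left unstandardized, so what is judged will vary between surgeons.
- The Discussion offers required consensus as protection against unblinded adjudication, whereas the adjudication section allows a vote.

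**2. Event base: reproducing the plan's figure.** Inputs are from Sample size determination: 1,441 patients (720.5 per arm), year 1 revision risk 25%, relative risk reduction (RRR) 25%, mortality 15% then 10%, loss 5% in each year, year 2 hazard one-third of year 1. Let h = −ln(1 − revision risk) and c = −ln(1 − mortality) − ln(1 − loss). Events per patient in a year = h/(h + c) × [1 − exp(−(h + c))].
- Cancellous screws, year 1: h = 0.2877, c = 0.2138, giving 0.2262 × 720.5 = 163.0.
- Sliding hip screw, year 1: 122.1. Year 2: 37.0 and 30.0.
- Total 352.1, against 353 stated.

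For the 1,000-patient design (risks 15.5% and 27.2%, mortality 11.0% and 18.2%, loss 12.2% and 5.9%, RRR 30%), the same method gives 148.5 and 106.8 events, about 255 in all.

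**3. Range for the 24-month risk.** The plan calls 27.2% the annual rate for year 2. Combined with 15.5% in year 1, the risk is 1 − (0.845 × 0.728) = 38.5%. The low end is the pooled literature risk of 22.7%. The article gives no time horizon for that figure, so its use here is an assumption.

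**4. Shift from unequal exclusion.** The exclusion rates are assumed.
- One percentage point excluded in one arm only: 0.01/0.227 = 4.4 points of RRR; 0.01/0.385 = 2.6 points.
- 3% against 1% excluded, equal true risk: (0.227 − 0.03)/(0.227 − 0.01) = 0.197/0.217 = 0.91; (0.385 − 0.03)/(0.385 − 0.01) = 0.355/0.375 = 0.95.

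**5. Bias or power?** Power = Φ(½√D × |ln HR| − 1.96), with D the events × 0.932 for crossover.
- Equal exclusion in both arms, RRR 30%: HR = ln(1 − 0.7 × 0.155)/ln(1 − 0.155) = 0.682. Power is 84.0% with none excluded, and 83.2%, 82.1% and 80.0% with 2%, 5% and 10% of events excluded. (Table 3 states 86.3%; without a crossover allowance the formula gives 86.4%.)
- Exclusion in one arm only, true HR 1, 148.5 events per arm before exclusion: losing 2%, 5% or 10% of that arm's events gives an apparent HR of about 0.98, 0.95 or 0.90. The chance of a significant result in that direction is about 3.7%, 6.2% or 13.4%, against 2.5% nominal. For 5%: D = 2 × 148.5 × 0.975 × 0.932 = 269.8, and Φ(8.21 × 0.0513 − 1.96) = 6.2%.

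**The case against.** The rule is pre-specified, applies to both arms, and is applied by several surgeons blinded to site. The Discussion admits the lack of blinding openly. Working definitions may sit in an adjudication charter that the article condenses. The only early timing figure in the article is that all revisions of undisplaced fractures in previous studies fell between 2 and 12 months, which suggests that very early revisions are few. Those studies may have used similar exclusions, however, and displaced fractures may differ.

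A reader might infer that implant-related failures are being removed after the fact. The documents do not support that. They call the malreduction technical. The contamination section treats reduction as obtained for placement of the implant, and the torsional-stability contrast in the Background concerns the fixed construct. Implant failure, hip instability and nonunion are all counted reasons for revision. Nothing says that malreduction differs by arm.

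A reader might also take 27.2% as the 24-month risk. The plan labels it the year 2 annual rate. It would give 0.01/0.272 = 3.7 points per percentage point, which lies inside the range shown.

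The objection limits the size and the causal story. It does not remove the conflict between the exclusion and the objectivity argument, because that conflict lies in what the article states.

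**Conclusion.** The point holds as a gap in protection against bias, not as evidence that bias exists. The endpoint section removes re-operations that can meet its own event list, on a judgement of surgical quality made by adjudicators who know the arm, with no test of relatedness to allocation. The Discussion's defence covers the occurrence of re-operation and not this decision.

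The size cannot be computed from the documents, because they give no count of such revisions. The 3% and 1% exclusion rates and the 2% to 10% shares are assumptions. Within them, a spurious risk ratio of about 0.91 to 0.95 is possible under no true difference, while equal exclusion costs at most about 4 points of power. The change should be made, since it is cheap and protects the primary comparison.

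**What to change.** Restrict planned revisions to re-operations documented as scheduled before the index operation began. Count early revision for malreduction as an event where it meets the endpoint's existing purpose and procedure criteria. Implant removal should still count only before fracture healing. Counting every re-operation on the hip would go too far, because it would drop the purpose test and that limit.

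If the primary definition is not to be changed now that 589 patients have completed follow-up, pre-specify, before any unblinded comparison, a sensitivity Cox analysis that counts these revisions as events. In either case, report the number of excluded revisions by arm, and limit the Discussion's statement on objectivity to the occurrence of re-operation.

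The cost is a wording change, one further analysis if the second route is taken, and re-coding of some events already adjudicated. Counting these revisions also brings some surgeon-technique events into the endpoint, which adds a little noise.

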#### *Secondary study endpoints*

The secondary study endpoints include: (1) Health-related quality of life; (2) Functional outcomes; (3) Health state utilities; (4) Fracture healing; (5) Mortality; and (6) Other adverse events such as avascular necrosis, non-union, malunion, implant breakage or failure, and infection. Health-related quality of life will be measured by the Short Form-12 (SF-12) [32], the EuroQol-5 Dimensions (EQ-5D) [33], and the Western Ontario and McMaster Universities Arthritis Index (WOMAC) [34].

The SF-12 is a 12-item questionnaire that measures health-related quality of life across 8 domains. Both physical and mental summary scores can be obtained. Each domain is scored separately from 0 (lowest level) to 100 (highest level). The instrument has been extensively validated and has demonstrated good construct validity, high internal consistency, and high test-retest reliability [35] and is frequently used in orthopedics for evaluating fracture outcomes.

The WOMAC index is self-administered and assesses the three dimensions of pain, disability and joint stiffness in knee and hip osteoarthritis using a battery of 24 questions [34]. It is a valid, reliable and responsive measure of outcome, and has been used in several studies involving a wide range of lower extremity conditions [36].

The EQ-5D is a comprehensive, compact health status classification and health state preference system [33]. This questionnaire is widely used and has demonstrated validity and sensitivity in many populations [33,35].

### Adjudication of study events

The CAC is comprised of a Chairperson plus three orthopaedic surgeon committee members. The CAC is responsible for assessing patient eligibility (if in doubt) and they will independently adjudicate radiographic characteristics and quality of the surgery, fracture healing, revision surgeries, fracture-related complications (i.e., avascular necrosis, nonunion, malunion, implant breakage or failure, infection), and mortality. The adjudicators may review the patients’ case report forms and x-rays and determine if the reported outcome meets the criteria for being a study event. Any disagreements between the adjudicators will be discussed and resolved during consensus conference calls with the CAC. If consensus cannot be reached after extensive discussion, a vote will be permitted at the discretion of the Chair. All decisions made by the committee will be final. The CAC members will not be blinded to treatment as it is not possible to accurately judge blinded images; however, they will be blinded to the name and location of the clinical site.

### Study follow-up

Table 1 shows the schedule of study follow-up events. At each follow-up, study outcomes will be recorded. Any revision surgeries and adverse events will be recorded at each visit. Missed follow-up visits or early withdrawal will also be documented.We will only withdraw patients for the following scenarios: (1) Patients withdraw consent for participation; or (2) Patients are deemed lost to follow-up after the 24 month visit is overdue and all exhaustive measures have been taken to locate the patient (see Figure 2 for a detailed depiction of methodology for limiting loss to follow-up). We will document the reasons for patient withdrawal from the trial. For those patients who withdraw from other study activities, we will seek their approval to collect clinical data from their medical and hospital charts, and/or to contact them by telephone to ask about the primary and secondary outcomes. We will not withdraw patients even if the study protocol was not adhered to (e.g., patient received wrong treatment arm, occurrence of protocol deviations, missed follow-up visits, etc.).

**Table 1 T1:** Schedule of events

**Radiographs & event forms**	**Pre-surgery**			**Surgery**	**Post-surgery**								
	**Screening**	**Enrolment**	**Baseline**	**(Day 0)**	**≤ 48 hrs Post surgery**	**D/C**	**1 wk (24 hrs-10 ds)**	**10 wk (8-12 wks)**	**6 mo (5-7 mos)**	**9 mo (8-10 mos)**	**12 mo (11-13 mos)**	**18 mo (17-19 mos)**	**24 mo (≥24 mos)**
**Radiographs**			**●**		**●**			**●**			**●**		**●**
**Screening**	**●**												
**Informed consent**		**●**											
**Randomization**		**●**											
**Baseline**			**●**										
**Patient contact**		**●**			**●**	**●**	**●**	**●**	**●**	**●**	**●**	**●**	**●**
**Pre-Op care**			**●**										
**Fracture characteristics**			**●**										
**Surgical report**				**●**									
**Post-Op care**					**●**								
**Clinic or telephone follow-up**							**●**	**●**	**●**	**●**	**●**	**●**	**●**
**RS**					*****		*****	*****	*****	*****	*****	*****	*****
**AE**				*****	*****		*****	*****	*****	*****	*****	*****	*****
**Hospital D/C**						**●**	*****	*****					
